| STATISTICAL METHODS AND EVALUATION OF DATA | 
Demographic data of each study group will be tabulated.
 
Safety data: Listings will be made of the safety data collected at each time point. Descriptive statistics will be used to analyze adverse events (AEs) including intercurrent illnesses. The numbers of AEs and their severity will be reported using frequency tables. With frequently occurring (10 or more) event types, effects of dose and vaccine will be tested by recording the presence/absence of the event in each patient and using logistic regression models to test for differences between groups.
 
Immunogenicity data: Immunological data for each time point will be analyzed separately.
 
 
Descriptive statistics (minimum, maximum, median, geometric mean, arithmetic mean and quartiles) will be computed for each immunological measure and each time point, separately for each group.
 
For each volunteer, the ratio of the immunological measure to that assessed at baseline (during screening) will be computed. Descriptive statistics of these ratios (minimum, maximum, median, geometric mean, and quartiles) will be computed for each immunological measure and each time point, separately for each group.
 
Wilcoxon test will be used to compare the immunological measures between doses and between group E and groups C or D (as appropriate) for each immunological measure, each time point and each antigen.
 
                                                                                                                                                                                                                                                                                                                                                                                                                                                                                                                                                                                                                                                                                                                                                                                                                                                                                                                                                                                                                                                                                                                                                                                                                                                                                                                                                                                                                                                                                                                                                                              |                     |                                                                                                                                                          |                 |                                          |

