## 3 Study Design

This prospective phase I, single centre, randomized, single blind, placebo controlled, dose escalating study will be conducted in 46 healthy adult volunteers. Eligible study participants will be randomized into six groups: PEV 301 10 µg (group A, n = 8) or PEV 302 10 µg (group B, n = 8) or PEV 301 50 µg (group C, n = 8) or PEV 302 50 µg (group D n = 8) or PEV 301 50 µg plus PEV 302 50 µg (group E, n = 8) or virosomes alone (group F, n = 6).

Study participants will be vaccinated three times, i.e. at days 1, 64(+2) and 183(+2) and followed-up 3 times after each vaccination. If any of the study groups does not show any immune response 3 weeks after the 2nd vaccination, no 3rd vaccination will be given to that group, i.e. the study for that group will be terminated 3 weeks after the 2nd vaccination.

Groups C & D (PEV 301 50 µg; PEV 302 50 µg) will be started 5 weeks after the 1st vaccination of groups A, B.

Group E (PEV 301 plus PEV 302) will be started 5 weeks after the 2nd vaccination of groups C and D.

Group F will be distributed and serve as a control in all groups receiving the active product.

The total duration of the study for each participant is 31 weeks, the number of visits is 13.

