### 8.3 Recording adverse events

At each visit/assessment, all adverse events either observed by the investigator or one of his clinical collaborators or reported by the subject spontaneously or in response to a direct question will be evaluated by the investigator. Adverse events not previously documented in the diary card will be recorded in the Adverse Event form within the subjects CRF. The nature of each event, date and time (where appropriate) of onset, outcome, intensity and relationship to vaccination should be established. Details of any symptomatic/corrective treatment should be recorded on the appropriate page of the CRF.

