#### General adverse events

This is the first study in men with PEV 301 and PEV 302, therefore, general solicited adverse events related to PEV 301 and PEV 302 will be determined in this study.

As a consistent method of soliciting adverse events, the subject should be asked a non-leading question such as:

"Have you felt different since receiving the vaccine or since the previous visit?"

Adverse events already documented in the CRF, i.e. at a previous assessment, and designated as 'ongoing' should be reviewed at subsequent visits, as necessary. If these have resolved, the documentation in the CRF should be completed. If an adverse event changes significantly in frequency or intensity during a study period, a new record of the event will be started.

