## 8.4 Assessment of intensity

Intensity of the following local adverse events should be assessed as described:

| Adverse Event | intensity grade | Parameter                  |
|---------------|-----------------|----------------------------|
| Pain          | 0               | Absent                     |
|               | 1               | Painful on touch           |
|               | 2               | Painful when limb is moved |
|               | 3               | Spontaneously painful      |
| Redness       | 0               | Absent                     |
|               | 1               | >5 mm                      |
|               | 2               | >20 mm                     |
|               | 3               | >50 mm                     |
| Swelling      | 0               | Absent                     |
|               | 1               | >5 mm                      |
|               | 2               | >20 mm                     |
|               | 3               | >50 mm                     |

For all other adverse events, grading and reporting has to be done according to Common Terminology Criteria for Adverse Events v3.0 (CTCAE). This document will be provided to the CRC of the Kantonsspital Basel by STI-PMU as part of the Investigator Folder.

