#### Safety data:

Listings will be made of the safety data collected at each time point.

Descriptive statistics will be used to analyze adverse events (AEs) including intercurrent illnesses. The number of AEs and their severity will be reported using frequency tables. With frequently occurring (10 or more) event types, effects of dose and vaccine will be tested by

recording the presence/absence of the event in each patient and using logistic regression models to test for differences between groups.

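### Section 10.6 tabulates adverse events and triggers tests at an unlabelled ten or more, while the test it triggers counts volunteers

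*Protocol*

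**What the plan says.** The safety paragraph of section 10.6 fixes three things.

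- The unit of the tables is the event: "The number of AEs and their severity will be reported using frequency tables". The synopsis has the same sentence ("The numbers of AEs and their severity will be reported using frequency tables").
- The selection rule has no unit: "With frequently occurring (10 or more) event types, effects of dose and vaccine will be tested by" a model.
- The unit of that model is the volunteer: "recording the presence/absence of the event in each patient and using logistic regression models to test for differences between groups".

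Section 3 sets three vaccinations per person, with participants "followed-up 3 times after each vaccination". It also sets five active groups of 8 and a virosome group of 6.

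On data collection, section 8.3.1 (General adverse events) adds: "If an adverse event changes significantly in frequency or intensity during a study period, a new record of the event will be started". Section 8.3 limits what reaches the adverse event form: "Adverse events not previously documented in the diary card will be recorded in the Adverse Event form within the subjects CRF". Section 8.4 grades pain, redness and swelling from 0 to 3, and then states: "For all other adverse events, grading and reporting has to be done according to Common Terminology Criteria for Adverse Events v3.0 (CTCAE").

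**The concern.** Safety is the primary objective, and section 10.5 justifies groups of 8 by how well they estimate adverse event frequency. That purpose calls for a proportion of volunteers. A count of events has no such denominator, and over three injections it mixes how many people react with how often each one reacts.

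The selection rule inherits the problem. If ten means events, the rule rewards recurrence in a few people, whereas the test sees only how many people are affected. If ten means volunteers, the number exceeds the size of any single group. On either reading, the threshold can exclude the pattern a dose-escalation trial most needs to examine: an event concentrated in one group, for example the combination group E.

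**Working it through.** **Inputs.** Groups of 8, 8, 8, 8, 8 and 6; three injections per volunteer (section 3); threshold 10 (section 10.6). The head count reproduces: 5 × 8 + 6 = 46, and by recruitment wave 18 + 18 + 10 = 46 (section 6.3). The protocol gives no derivation for the threshold of 10, so there is no plan figure to reproduce for it.

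**Step 1: ten read as events.** With one event after each injection, a volunteer contributes 3. The smallest number of volunteers reaching the trigger is ceil(10/3) = 4, giving 4 × 3 = 12 events; three volunteers give only 9. An event affecting all 8 volunteers of one group once, and nobody else, gives 8, so it is not tested.

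**Step 2: ten read as volunteers.** The largest count for an event confined to one active group is 8, which is below 10. It can never be tested, however often it recurs.

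**Step 3: what is left untested.** When all k affected volunteers are in one of two groups of 8, the two-sided Fisher p-value is 2 × C(8,k) / C(16,k):

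| k/8 vs 0/8 | calculation | p |
|---|---|---|
| 4 | 2 × 70 / 1820 | 0.077 |
| 5 | 2 × 56 / 4368 | 0.026 |
| 8 | 2 × 1 / 12870 | 0.0002 |

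Patterns from 5/8 to 8/8, once each and with no events elsewhere, would therefore separate two groups at 5% but stay below the trigger on either reading. For the pooled dose contrast (16 at 10 µg vs 16 at 50 µg), 0/16 vs 4/16 gives p = 0.101 and 0/16 vs 5/16 gives p = 0.043, so 5 is again the smallest number.

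**Step 4: how much the reading matters.** The protocol states no event rates, so per-volunteer incidences are assumed here. The binomial chance, out of 46, that enough volunteers are affected is:

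| assumed incidence | at least 10 affected | at least 4 affected |
|---|---|---|
| 5% | 0.000 | 0.197 |
| 10% | 0.014 | 0.688 |
| 20% | 0.441 | 0.989 |
| 30% | 0.921 | 1.000 |

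The last column meets an event-based trigger only if every affected volunteer has three events, so it marks the far end of the range.

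**Step 5: additional records.** Records per episode = 1 + number of changes treated as significant. Grades 1-2-1 give 3 records; 1-2-3-2-1 give 5. If records were counted as events, three per injection over three injections would be 9 per volunteer, and ceil(10/9) = 2 volunteers would reach the trigger. This step depends on a counting rule that the protocol does not state.

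**The case against.** A reader might infer that one reaction which rises and falls is counted as three adverse events. The documents do not support this.

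- Section 8.3.1 opens a further record of the same event, and section 10.6 counts events, not records. Section 8.1 treats a discrete episode as the reportable unit for chronic conditions.
- The rule sits in a paragraph on events already in the CRF, marked ongoing and reviewed at later visits. Those visits are days apart, and section 8.3 keeps events already on the diary card off the adverse event form. A short reaction in the first four days may never be split.
- Only a significant change opens a record, and that word is not defined. Three is not a ceiling either.
- Joining records into episodes is commonly left to a statistical analysis plan, which is not at hand.
- Presence/absence per volunteer is the same however many records exist.

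All of this stands, so inflation from extra records is only a conditional addition.

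Against the rest of the point, four things can be said. First, the threshold sentence goes on to speak of each patient, so a volunteer count is a possible reading. That is fair, but Step 2 shows that this reading has its own gap; and where the protocol means people it says so, as in sections 9.4 and 10.4. Second, an 8/8 event stays untested on the event reading only if it hardly recurs and is nearly absent elsewhere (a total of at most 9), and it would still appear in the tables and listings. That is true, and it limits the harm. Third, with 8/8 vs 0/8 the logistic model has no finite estimate, so a lower trigger alone would not help. That is correct, and the fix must name a test for this case. Fourth, the protocol plans no Fisher test, and section 10.5 says that group differences are not powered. That is also correct: a cut-off of 5 is an example, not a derived requirement.

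**Conclusion.** The point holds in limited form and is minor. Section 10.6 and the synopsis state the safety tables in events, set a trigger of ten with no unit, and attach it to a test in volunteers. As few as 4 of 46 volunteers can trigger the test on the event reading. An event in all 8 of one group, once each and nowhere else, goes untested on both readings.

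The effect is confined to how the tables read and which exploratory tests are run; no test result is biased by it. The Fisher figures assume a two-group comparison of 8 vs 8 or 16 vs 16, and the incidences in Step 4 are assumptions. Whether the section 8.3.1 records add to the counts cannot be settled from the protocol.

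**What to change.** In section 10.6 and the synopsis:

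1. Tabulate, per group, the number and proportion of volunteers with at least one event of each type, overall and per injection, at worst intensity. Give the number of episodes alongside, with all records of one ongoing event counted as one episode.
2. State the testing trigger as a number of volunteers with the event, no larger than one group. Five is a workable example, because it is the smallest number at which 8 vs 8 can reach two-sided 5% by Fisher's exact test.
3. Name in advance an exact or likelihood-ratio test for comparisons where a group has no affected volunteers or only affected ones. The choice matters at these sizes: 0/16 vs 4/16 gives p = 0.101 by Fisher and 0.013 by likelihood ratio.

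Keep the section 8.3.1 record rule for data collection. The cost is a wording change and a simple derivation from data already collected. The downside is a few more exploratory p-values in a trial not powered for group differences.

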#### 8.3.2 Unsolicited adverse events

Unsolicited symptoms are adverse events, reported by the subjects, which begin after the 4 day follow-up period for solicited symptoms. Space on the diary card and CRF will be allocated for the recording of unsolicited symptoms. Should any systemic (general) signs or symptoms be reported, their relationship with the study vaccine will be assessed by the investigator and transcribed into the CRF.

## 8.4 Assessment of intensity

Intensity of the following local adverse events should be assessed as described:

| Adverse Event | intensity grade | Parameter                  |
|---------------|-----------------|----------------------------|
| Pain          | 0               | Absent                     |
|               | 1               | Painful on touch           |
|               | 2               | Painful when limb is moved |
|               | 3               | Spontaneously painful      |
| Redness       | 0               | Absent                     |
|               | 1               | >5 mm                      |
|               | 2               | >20 mm                     |
|               | 3               | >50 mm                     |
| Swelling      | 0               | Absent                     |
|               | 1               | >5 mm                      |
|               | 2               | >20 mm                     |
|               | 3               | >50 mm                     |

For all other adverse events, grading and reporting has to be done according to Common Terminology Criteria for Adverse Events v3.0 (CTCAE). This document will be provided to the CRC of the Kantonsspital Basel by STI-PMU as part of the Investigator Folder.

## 8.5 Assessment of causality

Every effort should be made by the investigator to explain each adverse event and assess its causal relationship, if any, to administration of the study vaccine(s).

The degree of certainty with which an adverse event can be attributed to administration of the study vaccine(s) (or alternative causes, e.g. natural history of the underlying diseases, concomitant therapy, etc.) will be determined by how well the event can be understood in terms of one or more of the following:

- Reaction of similar nature having previously been observed with this type of vaccine and/or formulation.
- The event having often been reported in literature for similar types of vaccines.
- The event being temporally associated with vaccination or reproduced on re-vaccination.

All solicited reactions will be considered related to vaccination. Causality of all other adverse events should be assessed by the investigator using the following method:

In your opinion, is there a reasonable possibility that the adverse event may have been caused by the study vaccine(s)?

|          |                                                                                                                                                                                                                 |
|----------|-----------------------------------------------------------------------------------------------------------------------------------------------------------------------------------------------------------------|
| Related  | suspicion that there is a relationship between vaccine and AE (without determining the extent of probability); there is a reasonable possibility that the vaccine contributed to the AE                         |
| Probable | AE occurs within a reasonable time after the administration of the vaccination and cannot be reasonably explained by other factors (i.e. clinical condition, environmental / toxic factors or other treatments) |
| Possible | AE occurs within a reasonable time after the administration of the vaccine but can also be reasonably explained by other factors (as mentioned above)                                                           |
| Unlikely | AE does not occur within a reasonable time after the administration of the vaccine (unusual time frame) and can also be reasonably explained by other factors (as mentioned above)                              |

Unrelated      there is no suspicion that there is a relationship between vaccine and adverse event, there are other more likely causes and administration of the study vaccine is not suspected to have contributed to the AE

Non-serious and serious adverse events will be evaluated as two distinct types of events given their different medical nature. If an event meets the criteria to be determined "serious" (see Section 9.1 for definition of serious adverse event), it will be examined by the investigator to the extent to be able to determine ALL contributing factors applicable to each serious adverse event.

Other possible contributors include:

- Underlying disease
- Other medication
- Protocol required procedure
- Other cause (specify)

## **8.6 Follow-up of adverse events and assessment of outcome**

Investigators should follow-up non-serious adverse events until the end of the study.

Outcome should be assessed as:

- 1      = Resolved
- 2      = Resolved with sequelae
- 3      = Ongoing at subject study conclusion
- 4      = Died
- 5      = Lost to follow up

## **8.7 Reporting of adverse events**

All adverse events occurring within one month (minimum 30 days) following administration of each dose of vaccine must be recorded on the adverse event form in the subject's CRF, irrespective of severity or whether or not they are considered vaccination-related.

At each visit/assessment, all adverse events, either observed by the investigator or one of his clinical collaborators or reported by the subject spontaneously or in response to a direct question will be evaluated by the investigator. Adverse events not previously documented in the study will be recorded in the AE form within the subject's CRF. The nature of each event, date and time (where appropriate) of onset, outcome, intensity and relationship to vaccination should be established. Details of any corrective treatment should be recorded on the appropriate page of the CRF.

## **8.8 Reporting of serious adverse events**

All Serious Adverse Events (SAEs) must be reported immediately by the investigator without filtration, whether considered to be associated with the study vaccine, active comparator or placebo and whether or not considered vaccination related. The investigator must report SAEs within one calendar day of becoming aware of the event by telephone, telefax or e-mail (if appropriate) to the Study Contact for Reporting Serious Adverse Events as described below. This initial notification should include minimal, but sufficient information to permit identification of the reporter, the subject, the study vaccine, adverse events, and date of onset. The investigator should not wait for additional information to fully document the event before notifying. The responsible monitor will confirm this first notification. The report is then to be followed by submission of a completed SAE Report Form provided by STI/PMU as soon as possible but at latest within 3 calendar days of the initial telephone / telefax or e-mail report detailing relevant aspects of the adverse events in question. All actions taken by the investigator and the outcome of the event must also be reported immediately. For

documentation of the SAE and, any actions taken, for outcome and follow-up reports the SAE Report Forms are to be used. Where applicable, hospital case records and autopsy reports should be obtained.

Investigators must report SAEs to the Ethikkommission beider Basel according to the “Richtlinien bezüglich der Meldung von Serious Adverse Events (SAE) an die EKBB” as published on the webpage of the EKBB ([www.ekbb.ch](http://www.ekbb.ch)).

| Study Contact for Reporting Serious Adverse Events
24/24 hour and 7/7 days availability                                                                                                 |
|----------------------------------------------------------------------------------------------------------------------------------------------------------------------------------------------------------|
| Name, address: [name], Schweizerisches Tropeninstitut
[contact]
[contact]
Outside office hours
[contact]
Mobile [contact] |
| Back-up Study Contact for Reporting Serious Adverse Events                                                                                                                                        |
